## Methods / design

### Study design

The APROPOS-II study uses a hybrid effectiveness-implementation design [14, 15]. In a stepped-wedge cluster-randomized controlled trial (RCT) we will implement and evaluate the effectiveness of the intervention. Randomization occurs at a cluster-level instead of an individual-level because the intervention has a community-approach in which the entire target population will be exposed to the intervention. All participating municipalities start with a control-phase, which will last 6–16 months depending on randomization order. The total duration of the study is 30 months (Fig. 1). The RE-AIM (reach, effectiveness, adoption, implementation, maintenance) framework will be used to evaluate the intervention and the implementation strategy [16].

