### Statistical analysis

Statistical analysis will be performed using multilevel logistic regression analysis to take into account the clustering of respondents within municipalities. Data will be analysed anonymously on two levels; the respondents’ level (before and after the intervention) and the municipal level (differences between municipalities). Baseline characteristics will be compared between the pre- and post-intervention group and compared in a baseline table. Chi-square analysis and ANCOVA will be used to study the effects of the intervention on the adverse pregnancy outcomes. Adjusted odds ratios will be calculated taking into account the potential confounders: age, educational level and parity. *P*-values < 0.05 are considered statistically significant.

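### The stated stepped-wedge analysis has no calendar-time term, so a secular trend in preconception behaviour would bias the primary odds ratio

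*Protocol article*

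**What the plan says.** Under Study design, the protocol article states: "In a stepped-wedge cluster-randomized controlled trial (RCT) we will implement and evaluate the effectiveness of the intervention". The rollout goes one way: "All participating municipalities start with a control-phase, which will last 6–16 months depending on randomization order". It adds: "The total duration of the study is 30 months".

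Under Statistical analysis, the model is given with its purpose: "Statistical analysis will be performed using multilevel logistic regression analysis to take into account the clustering of respondents within municipalities". The two levels of analysis are "the respondents’ level (before and after the intervention) and the municipal level (differences between municipalities". Baseline characteristics are compared between the pre- and post-intervention groups, and adverse pregnancy outcomes are to be examined by chi-square tests and ANCOVA. The covariates named are age, educational level and parity: "Adjusted odds ratios will be calculated taking into account the potential confounders: age, educational level and parity".

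Neither section mentions period, step, calendar month or secular trend as part of the analysis, and no other section does.

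**The concern.** In a stepped wedge, each municipality's control data come first and its intervention data later. A comparison of before with after inside municipalities therefore mixes the intervention effect with whatever changed over the same months. The staggered, randomised crossover separates the two, but only if the model contains time. Municipalities that have crossed can then be compared with those that have not in the same period. A model with a municipality effect and patient covariates alone makes no use of that comparison.

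The primary odds ratio and its p-value are at stake. A rising trend would look like benefit, and a falling one would hide it. The Discussion ties a positive result to national or international upscaling.

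**Working it through.** **Inputs from the article.** Six municipalities; control phase 6–16 months; total duration 30 months; target OR 1.5; alpha 0.05; power 80%; ICC 0.02; 363 women per municipality, 2167 in total, 23 per month per municipality.

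**Assumptions.** Crossovers at months 6, 8, 10, 12, 14 and 16 (the timeline figure is not shown); two-sided test; even recruitment; control proportion 0.20–0.70, because none is stated; all trend sizes.

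**The stated sample size.** It cannot be reproduced from the article alone, because the control proportion is missing. Under a stepped-wedge linear mixed model with six clusters, seven equally filled periods and one crossover per step, the N needed for 80% power is:

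| Control proportion | With period effects | Without period effects |
|---|---|---|
| 0.40 | 2204 | 930 |
| 0.45 | 2180 | 920 |
| 0.50 | 2204 | 930 |

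The stated 2167 is close to the time-adjusted column at mid-range proportions. Without period effects, an N near 2167 would need a control proportion of roughly 0.10.

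**How much trend enters the estimate.** Let recruitment be even over T months and a municipality cross at month c, with c < T. Mean control time is c/2 and mean intervention time is (c + T)/2. The gap is (c + T)/2 − c/2 = T/2, whatever c is. A linear trend on the log-odds scale therefore passes about half of its change over the window into the before/after estimate. For T = 30:

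- whole-study trend OR 1.10: √1.10 = 1.05
- OR 1.25: √1.25 = 1.12
- OR 1.50: √1.50 = 1.22

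**Simulation under a true intervention OR of 1.** About 2178 women (6 × 363), control proportion 0.3 or 0.5, recruitment windows of 18, 24 and 30 months with the trend defined over the window, and 600 replicates per scenario. The logistic model used fixed municipality effects as an approximation to the random intercept.

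| Trend over window (OR) | Apparent OR, no time term | Rejection, no time term |
|---|---|---|
| none | about 1.00 | 4–6% |
| 1.10 | about 1.05 | 7–10% |
| 1.25 | about 1.12 | 17–24% |
| 1.50 | about 1.22 | 47–61% |

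With two-month period effects added, the estimated OR is 0.99–1.02 and rejection is 4–7% in every scenario. Monte Carlo error is about ±2 points near 5% and ±4 points near 50%.

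**Shorter recruitment window.** The article does not say that recruitment fills all 30 months; 363/23 = 15.8 months at the stated rate. Hold the trend at OR 1.25 per 30 months and let the window shorten. The gap falls to T/2 and the spurious OR to 1.25^(T/60): 1.12 at T = 30, 1.09 at T = 24 and 1.07 at T = 18. The bias shrinks but does not vanish.

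**Power after the fix, N = 2167.** In the seven-period design with equal recruitment per period, power is 66%, 76%, 79%, 79%, 76% and 69% at control proportions 0.20, 0.30, 0.40, 0.50, 0.60 and 0.70. With recruitment even over 30 months it is at most about 59%. That figure is the same with fifteen two-month periods as with seven step intervals (months 0–6, five of two months, 16–30). The loss comes from women recruited when all municipalities are in the same condition, not from the number of period terms.

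**The case against.** The strongest reply is that a short statistics paragraph in an article is not a model specification. It gives no equation and does not say that the covariate list is complete. The named confounders are respondent characteristics, while period is a design term that a full analysis plan could specify separately. The covariate sentence also follows the one on pregnancy outcomes and may apply only there. The match of 2167 with a time-adjusted calculation could even suggest that the authors planned with period effects and abbreviated the text.

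Some of this stands. A reader might infer that the plan deliberately excludes time or lists its full adjustment set; the wording does not establish either. It does state the model, its purpose, the contrast and named confounders, and an analyst following it would run a clustered before-after comparison. If the covariate sentence covers secondary outcomes only, the primary model has no stated covariates and still no time term. An unseen plan may repair this, but the published description would still need correcting.

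Three other stronger readings are not supported:

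- That exactly 15 months of trend enters in every municipality. This needs a linear trend and even recruitment over all 30 months; the latter is not stated and sits poorly with 23 women per month.
- That any trend is reported whole as an intervention effect. About half of a linear one is.
- That the cited sample-size method assumes time adjustment, so the trial was powered for another model. That source is not at hand, and the numerical match depends on an assumed control proportion.

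**Conclusion.** The point holds. As written, the analysis of a one-way stepped-wedge rollout omits the term that separates the intervention from calendar time. This is a fault in the stated analysis, beyond a detail left to a later document.

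The size depends on a trend that the article does not document. With no trend, the error rate is about nominal. A whole-study trend of OR 1.25 or 1.50 would yield a spurious OR of about 1.12 or 1.22 and false positives of 17–24% or 47–61%, set against a planned effect of OR 1.5. These figures rest on assumed trend sizes, linearity on the log-odds scale, even recruitment, two-month steps and control proportions of 0.3–0.5. The article gives no ground for saying that a trend exists or that a positive result would be false. It does leave the primary result unprotected if there is one.

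**What to change.** Add fixed calendar-period effects, one per step interval, to the primary multilevel logistic model next to the intervention indicator and the municipality effect. State that the intervention odds ratio from this model is the primary result.

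Adjust secondary outcomes for time as well, in place of unadjusted chi-square comparisons. Where events are sparse, such as congenital anomalies, use a more parsimonious time term, for example a linear one.

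The text change is small, but precision is lost: the confidence interval widens. Power should therefore be restated under the time-adjusted model, with the assumed control proportion and the expected distribution of recruitment over the study months. Under the assumptions above, it ranges from about 79% with equal recruitment per step period down to 59% or less with recruitment even over 30 months.

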## Discussion

The APROPOS-II study introduces a locally tailored PCC-approach in six municipalities in the Netherlands, that will contribute to current knowledge regarding the implementation and the effectiveness of PCC. Until now there is little data from randomized clinical trials that prove the effectiveness of PCC on maternal and perinatal health outcomes [3, 42, 43]. This evidence is necessary to substantiate the urgency to invest in a comprehensive (inter)national PCC-program. The presented intervention serves the different needs of prospective parents by providing both separate preconception health information and PCC-consultation. This supports the view that most prospective parents will benefit from evidence-based information to prepare themselves for pregnancy, while not every prospective parent will attend a PCC-consult.

Despite the low uptake of PCC-consults, the majority of prospective parents use the internet as their primary source of information regarding preconception health [11]. Women appreciate anonymity and self-management of online information in the privacy of their own home [11, 44]. The aim of the social marketing strategy in this intervention is to trigger women to actively prepare for their pregnancy by guiding them towards a website (www.wokewomen.nl) with practical and evidence-based information to help them improve their preconceptional health status. In addition, we encourage these women when there is a need for extra information to visit a healthcare provider for a PCC-consult.

Previous literature on social marketing strategies showed that it has the potential to improve diet, increase exercise and reduce substances-use like tobacco, and alcohol [18]. Creating a social movement could raise awareness on the importance of PCC and could cause a supportive social environment for preconception health. In addition, research shows that healthcare collaborations in health promotion can result in effective and sustainable benefits for those involved [45]. When effectively facilitated, healthcare collaborations can enable fundamental improvements to community development and health promotion.

Strengths of this stepped-wedge cluster RCT are the diversity of the population in the participating municipalities and the tailored intervention that complies with the heterogeneity of local settings. Moreover, the detailed questionnaire investigating respondents’ lifestyle behaviours, health beliefs and the extent of planning of the current pregnancy based on validated questionnaires can be considered a strength of this study. In addition, the innovative social marketing strategy, the extensive process evaluation and the involvement of the prospective father highlight different and often neglected aspects of PCC-research.

A potential limitation of this study is the occurrence of selection bias, as participants who have actively prepared for their pregnancy are probably more eager to share their experience. However, in our previous feasibility study, response rates were high and the population characteristics were similar before and after introduction of the intervention [13]. Another limitation is the selection strategy, as the respondents of this study are pregnant while the interventions focusses on the preconceptional period. Previous studies already showed that prospective parents are very difficult to identify and recruit, therefore almost all PCC related studies obtain information retrospectively [46]. Finally, active participation of the healthcare providers is crucial to make the local PCC-pathway a success. Fortunately, the healthcare providers involved in the local PCC-pathway are driven to improve the awareness of PCC in their municipality and will be equipped to provide adequate PCC. All community midwifery practices have already been recruited and municipal policy makers are involved throughout the entire project.

With this study, we expect to effectively implement and evaluate a locally tailored PCC-approach. If this intervention will show to improve lifestyle behaviours, leading to improved pregnancy outcomes and future health of prospective parents and their offspring, it may be upscaled to (inter)national implementation.

## Data Availability

Not applicable

## Abbreviations

LMUP: London Measure of Unplanned Pregnancy
NoMAD: Normalisation MeAsure Development
PCC: Preconception Care
RCT: Randomized Controlled Trial
RE-AIM: Reach, Effectiveness, Adoption, Implementation, Maintenance
WHO: World Health Organisation
